## Abstract

**Background:**

Effective diabetes prevention strategies that can be implemented in daily practice, without huge amounts of money and a lot of personnel are needed. The Dutch Diabetes Federation developed a protocol for coaching people with impaired fasting glucose (IFG; according to WHO criteria: 6.1 to 6.9 mmol/l) to a sustainable healthy lifestyle change: ‘*the road map towards diabetes prevention’* (abbreviated: Road Map: RM). This protocol is applied within a primary health care setting by a general practitioner and a practice nurse. The feasibility and (cost-) effectiveness of care provided according to the RM protocol will be evaluated.

**Methods/Design:**

A cluster randomised clinical trial is performed, with randomisation at the level of the general practices. Both opportunistic screening and active case finding took place among clients with high risk factors for diabetes. After IFG is diagnosed, motivated people in the intervention practices receive 3–4 consultations by the practice nurse within one year. During these consultations they are coached to increase the level of physical activity and healthy dietary habits. If necessary, participants are referred to a dietician, physiotherapist, lifestyle programs and/or local sports activities. The control group receives care as usual. The primary outcome measure in this study is change in Body Mass Index (BMI). Secondary outcome measures are waist circumference, physical activity, total and saturated fat intake, systolic blood pressure, blood glucose, total cholesterol, HDL cholesterol, triglycerides and behaviour determinants like risk perception, perceived knowledge and motivation. Based on a sample size calculation 120 people in each group are needed. Measurements are performed at baseline, and after one (post-intervention) and two years follow up. Anthropometrics and biochemical parameters are assessed in the practices and physical activity, food intake and their determinants by a validated questionnaire. The cost-effectiveness is estimated by using the Chronic Disease Model (CDM). Feasibility will be tested by interviews among health care professionals.

**Discussion:**

The results of the study will provide valuable information for both health care professionals and policy makers. If this study shows the RM to be both effective and cost-effective the protocol can be implemented on a large scale.

**Trial registration:**

ISRCTN41209683. Ethical approval number: NL31342.075.10.

## Background

Diabetes is an increasing problem which affects approximately 371 million people worldwide [1]. In 2011 the estimated prevalence in the Netherlands was 834.100 people with diabetes, of which 90% with type 2 diabetes mellitus (T2DM), with an annual estimate of newly discovered cases of 71,000 in that year [2]. This number translates into approximately 5% of the total Dutch population and is expected to rise to 1,300,000 and 1,600,000 in 2025 [3]. Many of these people are not aware of their risk of diabetes, but already have impaired fasting glucose (IFG; according to WHO criteria: 6.1 to 6.9 mmol/l). It is estimated, that some 750.000 people in the Netherlands between 30 and 70 years of age have either IFG or impaired glucose tolerance (IGT) [4]. People with IFG not only have a high risk of developing T2DM on short term, but also have an increased cardiovascular risk [5]. Without changes in lifestyle and proper support, about 9% of people with IFG will develop T2DM within three years [6].

When IFG is diagnosed, follow-up often is not well organized. The Diabetes Mellitus type 2 guideline of the Dutch College of General Practitioners 2006 advices a regular check in people known with IFG for development of T2DM and to treat their cardiovascular risk factors [7]. However, these people are not monitored systematically: most of the times a simple life style advice is given, combined with the advice to have fasting blood glucose measured at regular intervals. Health care providers indicate that there is a need for support in coaching people with IFG in a more systematic and intensive way. They also indicate that they do not know how to handle this group [8].

Lifestyle interventions which focus on both physical activity and diet can be effective for people diagnosed with IFG, with a relative risk reduction of 43% seven years after the start of the intervention [9,10]. Another study shows a similar risk reduction which sustained even 20 years after the start [11,12] Also Dutch projects show that it is possible to stimulate people to change their lifestyle [13-15]. For example, the SLIM study shows an improvement of glucose tolerance, which sustained after three years [16]. While the studies mentioned above show that a health gain can be achieved by people at risk for diabetes, another Dutch study on reducing risk by lifestyle change did not show the expected effects and proved to be not cost-effective [17]. Still it is concluded that combined lifestyle interventions are likely to have great potential as a strategy to prevent diabetes. Actually, these most successful interventions were obtained using many personnel and intensive supervision while the current practice requests less expensive, simple interventions which can be easily carried out in daily practice.

For above mentioned reason and in order to meet the needs of both people at high risk to develop T2DM and health care professionals, the Dutch Diabetes Federation (NDF) developed a protocol for coaching persons with an increased risk of diabetes in general practice called ‘*the road map towards diabetes prevention’* (abbreviated: Road Map: RM). It aims to delay or even prevent the development of T2DM and associated cardiovascular risk factors. The protocol is developed according to the framework of the Diabetes Mellitus type 2 Guideline of the Dutch College of General Practitioners [7]. To include people in the protocol, people at risk for diabetes were stimulated to fill out the Diabetes Risk Test (DRT). The DRT consists of ten questions covering risk factors for diabetes, and provides a score for the probability of developing diabetes within five years [9,18]. This paper describes the design of a RCT into the feasibility and (cost-) effectiveness of care provided according to the RM.

## Methods

### Study design

A clustered randomized controlled trial is carried out to study the feasibility and (cost-)effectiveness of the RM. Randomization takes place at the level of the general practices. The subjects in the intervention group are treated according to the RM. Persons in the control group receive care as usual, including one consultation each year, according to the T2DM guideline of the Dutch College of General Practitioners [7]. A baseline measurement takes place just after the diagnosis of IFG and just before the start of the intervention. Outcome measurements are performed one year after the diagnosis (t1, 1-year follow-up) and two years after the diagnosis (t2, 2-year follow up) (Figure 1).

**Figure 1 F1:**
[figure not shown]
Study design.

### Recruitment of general practices

Recruitment of general practices takes place in the North-eastern region of the Netherlands. Only practices which employ a practice nurse are included. Both, the general practitioner and the practice nurse are responsible for the recruitment and inclusion of participants.

### Recruitment of participants

Potential participants are selected by opportunistic screening and active case finding. Selection criteria for both are the absence of the diagnose diabetes and age (≥45). For opportunistic screening additional selection criteria are weight (BMI ≥ 25) and the presence of cardiovascular risk factors. Opportunistic screening takes place during consultations with the general practitioner and/or practice nurse. Active screening is based on the patient files in the general practices. Selected individuals receive a mailing in which they are asked to do the DRT at home or the DRT is filled out during the consultation. If the DRT shows an increased risk of T2DM, a fasting glucose measure has to be taken.

### Study population

All subjects diagnosed with IFG and motivated to change their lifestyle are included in the study. Exclusion criteria are previous education about IFG or diabetes, emotional, psychological or intellectual problems that are likely to limit the ability of the individual to comply with the protocol, malignant diseases or other diseases or conditions associated with a poor prognosis.

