### Training

The practice nurse carries out the intervention with support of the general practitioner, if necessary. Besides carrying out the RM, the practice nurses are responsible for the data collection. Prior to the start of the study, all practice nurses of the intervention group are trained to support them in applying the protocol. Additionally they are trained in techniques of motivational interviewing.

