### Randomisation

To avoid contamination of care as usual by the intervention, the randomisation takes place at the level of the general practices. General practices within the same health center are allocated to the same study group. A computerised random number generator is used to allocate the practices to the intervention or the control group.

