### Intervention

The RM protocol is based on the ‘stages of change’ model [19]. In this model change is considered as a process directed towards progress through a series of stages (precontemplation, contemplation, preparation, action and maintenance). The education and counselling of an individual persons’ needs depend on the stage he or she is in. People in the precontemplation and contemplation stage require information about the advances of a healthy lifestyle. People in the preparation stage are already aware of the advantages and disadvantages of a healthy lifestyle and require counselling and guidance to improve their ability to change their lifestyle. In the action stage, people do require tips and strategies for making the actual change. In the maintenance stage people may need additional guidance and feedback to stimulate them in maintaining their changed behaviour and to prevent relapse.

The first section of the protocol focuses on case finding and testing (Figure 2). The general practitioner is responsible for assessing subjects’ individual risk to develop T2DM. When someone is diagnosed with IFG, the second section of the RM is applied (Figure 3). This section of the protocol focuses on coaching the individual person to a healthy lifestyle. The practice nurse tries to get insight into the motivational situation of the participant. Based on this insight, three to four extra consultations spread over a one year period are carried out. During these consultations the practice nurse gives advice and teaches concrete and applicable skills in order to increase the level of physical activity and healthy dietary habits. If necessary, participants are referred to a dietician, physiotherapist, lifestyle programs and/or local sports activities. The practice nurse applies motivational interviewing techniques to determine someone’s motivational situation and to help a person to change his or her behaviour based on the model of stages of change [19,20]. After one year participants receive care as usual.

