#### Outcomes

The primary outcome measure in this study is change in Body Mass Index (BMI). Secondary outcome measurements are waist circumference, total and saturated fat intake, physical activity, systolic blood pressure, blood glucose, total cholesterol, triglycerides and the behaviour determinants risk perception, perceived knowledge, motivation, attitude, self efficacy and social norm.

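### Practice staff include people after allocation on an undefined motivation criterion, with only intervention nurses described as trained in motivational interviewing, so the arms can differ in motivation at entry

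*Protocol article*

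**What the plan says.** All references are to the protocol article.

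- **Unit of randomisation** (Randomisation): "To avoid contamination of care as usual by the intervention, the randomisation takes place at the level of the general practices".
- **Who includes participants** (Recruitment of general practices): "Both, the general practitioner and the practice nurse are responsible for the recruitment and inclusion of participants". Part of this happens face to face (Recruitment of participants): "Opportunistic screening takes place during consultations with the general practitioner and/or practice nurse".
- **Entry criterion** (Study population): "All subjects diagnosed with IFG and motivated to change their lifestyle are included in the study". The article does not say how motivation is assessed, by whom, or against what threshold. One exclusion, for emotional, psychological or intellectual problems thought likely to limit compliance, is also a judgement.
- **Training** (Training): "Prior to the start of the study, all practice nurses of the intervention group are trained to support them in applying the protocol". Then: "Additionally they are trained in techniques of motivational interviewing". No training of control nurses is described.
- **Adjustment** (Analysis, Effects): analyses adjust for baseline measurements and for possible baseline differences between the groups, and multilevel models handle clustering. Motivation is not named as a covariate.
- **Measurement of motivation**: it is a secondary outcome under Outcomes. The account of the questionnaires names self-efficacy, attitude and social norm, but not motivation.

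**The concern.** Randomising practices makes the practices comparable. It does not make comparable the people later chosen within them if those who choose know the arm and have discretion. Here the discretion falls on motivation, which the intervention, built on stages of change and motivational interviewing, itself treats as the key to behaviour change. A nurse trained to explore and raise motivation may class different people as motivated than a nurse without that training.

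If the included people differ in motivation, their BMI would change differently even if the Road Map did nothing, and the trial would read that difference as an intervention effect or as a lack of one. More participants or a multilevel model would not help, because neither changes who was selected.

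**Working it through.** **Step 1. Does the text allow differential selection?**

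1. Nurses of the intervention group are trained before the study starts, so practices had been allocated by then and those nurses know their arm. This is inferred from the timing. Whether control staff know theirs is not stated.
2. The general practitioner and nurse are responsible for inclusion, so it is inferred that they apply the motivation criterion. No independent or blinded recruiter is described.
3. The criterion is undefined in the article, and only the intervention nurses are described as trained in a skill that bears on it.

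Knowledge of allocation in one arm is enough for selection to differ between arms.

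**Step 2. Does the planned adjustment remove it?** Only in part. Motivation is not a named covariate and is not in the list of t0 questionnaire content. The questionnaire is handed out by the nurse after diagnosis, so in the intervention arm a trained nurse may already have influenced the answers. Nothing accounts for people with impaired fasting glucose who were not included.

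**Step 3. Reproduce the plan's own figure.** Inputs from Sample size calculation: difference 0.5 kg/m², SD 1.37, two-sided alpha 0.05, power 80%.

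n per group = 2 × [1.37 × (1.960 + 0.842) / 0.5]² = 117.9, so 118 before clustering. The article states 120 after allowing for an intra-cluster correlation of 0.011. That is close enough to use SD 1.37 and 120 per group below.

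SE of the difference = 1.37 × √(2/120) = 0.177. Unclustered power at 0.5 is Φ(0.5/0.177 − 1.960) = 80.7%.

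**Step 4. Illustrate the scale.** The document gives no input for this, so both of the following are assumptions:

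- r, the correlation of motivation with BMI change: 0.1 to 0.3
- d, the entry difference in motivation between arms, in SD units: 0.1 to 0.5

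Bias b = r × d × 1.37. With no true effect, the two-sided rejection rate is [1 − Φ(1.960 − b/SE)] + Φ(−1.960 − b/SE). If instead the true effect is 0.5 and the bias runs against the intervention, power is Φ((0.5 − b)/SE − 1.960).

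| r | d | b (kg/m²) | b as % of 0.5 | b/SE | Rejection rate, no true effect | Power if bias is against the intervention |
|---|---|---|---|---|---|---|
| 0.1 | 0.1 | 0.014 | 3% | 0.08 | 5.1% | 78.5% |
| 0.2 | 0.3 | 0.082 | 16% | 0.46 | 7.5% | 65.6% |
| 0.3 | 0.5 | 0.206 | 41% | 1.16 | 21.3% | 38.4% |

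Clustering changes little. With an assumed 10 participants per practice the design effect is 1 + 9 × 0.011 = 1.099, the SE becomes 0.185, and the highest rejection rate falls from 21.3% to 19.8%. The table takes no credit for baseline adjustment.

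**The case against.** The other side has several sound points.

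- **One criterion and one route.** Study population states a single criterion for everyone. It is about changing lifestyle, not about accepting coaching visits or a yearly check. Recruitment of participants describes a single path, not split by arm: age, no diabetes diagnosis, file selection or consultation, risk test, fasting glucose. A reader might infer from the Intervention section, where case finding is the first part of the Road Map, that control practices look for cases differently or apply a lower bar for motivation. The document does not say so. The objective gates also come first; judgement enters only at the last step.
- **More than baseline BMI is adjusted for.** The analysis section covers baseline measurements and observed group differences. Self-efficacy and attitude are in the questionnaires, and the process evaluation interviews a nurse in each practice about inclusion. This may reduce or reveal part of the problem. It does not measure motivation before contact with the nurse, or describe those left out.
- **Direction is unknown.** A reader might infer that the bias must favour the Road Map. It could equally run the other way: trained nurses may bring in less motivated people, and the Intervention section describes support for people in the precontemplation and contemplation stages.
- **An article condenses.** A motivation instrument or screening log may exist in the full protocol, so its absence here does not show that none exists. What stands is the design the article does fix: inclusion by practice staff after allocation, on motivation, with training in one arm before the study starts.

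**Conclusion.** The point holds as a risk that the stated design creates, not as a demonstrated bias. The arms can differ at entry in motivation, in either direction, and the planned adjustment cannot be relied on to remove the difference.

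The conclusion rests on two inferences (intervention staff know their arm when recruiting; practice staff judge motivation) and on the premise that motivation influences BMI change, which the document implies but does not quantify.

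The size is not estimable from the document. Over the assumed ranges it goes from trivial (about 0.01 kg/m²) to about 0.2 kg/m², two-fifths of the target. The matching unclustered type I error is about 5% to 21% if the bias favours the intervention. If it runs the other way, a real effect would be partly masked. A reader might infer that a positive result would be spurious; the figures do not support that, since the middle case moves the error rate only to 7.5%.

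**What to change.** 1. Use one fixed, self-completed motivation item, worded identically in both arms and answered before the nurse discusses inclusion, for example together with the Diabetes Risk Test.
2. Keep a log in every practice of all people found to have impaired fasting glucose: recruitment route, whether included, and if not, why.
3. Report inclusion fractions and baseline motivation by arm.
4. Prespecify a sensitivity analysis of BMI change that adjusts for the motivation item and for recruitment route (opportunistic or active).
5. For practices not yet started, complete the patient-file and mailing list before allocation is disclosed, where feasible. This cannot cover opportunistic screening, which runs through ordinary consultations, and the Abstract already describes screening in the past tense. Where allocation is already known, steps 2 and 3 still show whether selection differed, and steps 1 and 4 apply to people not yet screened.

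The cost is one extra item, one log per practice and a little more analysis. Step 5 would also delay disclosure and training in the practices concerned. These measures reduce or expose the bias; they do not guarantee its removal.

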### Training

The practice nurse carries out the intervention with support of the general practitioner, if necessary. Besides carrying out the RM, the practice nurses are responsible for the data collection. Prior to the start of the study, all practice nurses of the intervention group are trained to support them in applying the protocol. Additionally they are trained in techniques of motivational interviewing.

### Randomisation

To avoid contamination of care as usual by the intervention, the randomisation takes place at the level of the general practices. General practices within the same health center are allocated to the same study group. A computerised random number generator is used to allocate the practices to the intervention or the control group.

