#### Sample size calculation

The sample size calculation is estimated based on BMI with the objective to detect a decrease in BMI of 0.5 in the intervention group. In the SLIM study, the standard error of the mean in change in BMI was 0.2 kg/m2 and the standard deviation 1.37 [16]. The SLIM study has a comparable population to this study, so it is assumed that the standard error and standard deviations are also comparable. To adjust for clusters, an intra-cluster correlation of 0.011 is used [23]. Furthermore, a power of 80% and a two-sided alpha of 0.05 is used. Based on these assumptions, 120 people in each group are needed.

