#### Analysis

##### Effects

Multivariate variance and regression analysis are carried out to determine differences in effect on the primary and secondary outcome measures. All analyses are adjusted for baseline measurements and possible differences between both groups at baseline. To adjust for clustering, multilevel analyses are performed.

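### The general practice is named as the randomised unit, but practices sharing a health centre are allocated together; a multilevel model and ICC based on practice alone may understate the standard error

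*Protocol article*

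**What the plan says.** Study design states: "Randomization takes place at the level of the general practices". The abstract says the same. The Randomisation section gives avoidance of contamination as the reason and repeats that "the randomisation takes place at the level of the general practices". It then adds the constraint: "General practices within the same health center are allocated to the same study group". The next sentence again makes practices the objects being allocated: "A computerised random number generator is used to allocate the practices to the intervention or the control group".

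Two later places deal with clustering, and neither names a level:
- Sample size calculation: "To adjust for clusters, an intra-cluster correlation of 0.011 is used". No cluster size is given.
- Analysis, Effects: "To adjust for clustering, multilevel analyses are performed". The health centre is not mentioned.

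**The concern.** The variance of a treatment contrast in a cluster trial has to be built from the units that were allocated independently of one another. Two trial practices in the same centre receive one allocation between them, so together they supply one independent unit.

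The only cluster unit that the article names is the practice. An analyst who follows it would put practice at the top of the multilevel model. Where centres hold several trial practices, that model omits the level at which treatment was assigned. If participants in one centre resemble each other beyond sharing a practice, the model understates the standard error and overstates the degrees of freedom. Confidence intervals are then too narrow and the type I error exceeds 5%. A design effect computed from practice size would be too small for the same reason.

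**Working it through.** **Inputs from the Sample size calculation section.** The plan aims to "detect a decrease in BMI of 0.5 in the intervention group" (difference 0.5). From the SLIM study it takes the following: "the standard error of the mean in change in BMI was 0.2 kg/m2 and the standard deviation 1.37" (SD 1.37). Power is 80%, two-sided alpha 0.05, ICC 0.011, and 120 per group.

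**Inputs not in the article, therefore assumed.** Participants per practice m = 5 to 10. Trial practices per centre k = 2 to 3, the same in every centre. Share of the ICC lying between centres: none, half or all.

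**Step 1: the plan's own figure.** Without clustering, n per group = 2 × [1.37 × (1.960 + 0.842) / 0.5]² = 117.9, so 118. Multiplying by 1 + (m − 1) × 0.011 gives 120 at about 2.5 to 2.7 participants per cluster, about 123 at m = 5 and about 130 at m = 10. The stated 120 is reproduced, but it does not show which unit was meant by a cluster.

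**Step 2: variance factors.** Let ρ be the total within-practice ICC (0.011) and ρc the part of it that lies between centres.
- Practice as the only cluster level: Fp = 1 + (m − 1)ρ
- Allowing for joint allocation: Ft = 1 + (m − 1)ρ + (k − 1)mρc
- Ratio of the true to the practice-level standard error: r = √(Ft / Fp)
- Real two-sided alpha of a nominal 5% test: 2 × [1 − Φ(1.96 / r)]

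If k = 1 or ρc = 0, then Ft = Fp, r = 1.00 and alpha = 0.05.

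**Step 3: results at ρ = 0.011.**

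| m | k | Fp | Half between centres: Ft | r | alpha | All between centres: Ft | r | alpha |
|---|---|---|---|---|---|---|---|---|
| 5 | 2 | 1.044 | 1.0715 | 1.013 | 0.053 | 1.099 | 1.026 | 0.056 |
| 5 | 3 | 1.044 | 1.099 | 1.026 | 0.056 | 1.154 | 1.051 | 0.062 |
| 10 | 2 | 1.099 | 1.154 | 1.025 | 0.056 | 1.209 | 1.049 | 0.062 |
| 10 | 3 | 1.099 | 1.209 | 1.049 | 0.062 | 1.319 | 1.096 | 0.074 |

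Worked example for the last row: Ft = 1 + 9 × 0.011 + 2 × 10 × 0.011 = 1.319. Then r = √(1.319 / 1.099) = 1.096, and 2 × [1 − Φ(1.96 / 1.096)] is about 0.074.

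**Step 4: smaller clusters.** At m = 2.5, roughly the size implied by the stated 120, with all of the ICC between centres, r is 1.013 for k = 2 (alpha about 0.053) and 1.027 for k = 3 (about 0.056).

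**Step 5: power at 120 per group.** The effective n is 120 / F. With practice clustering only, power is 79% (m = 5) or 77% (m = 10). With the whole ICC between centres it runs from 77% (m = 5, k = 2) down to 69% (m = 10, k = 3).

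These alphas use the normal distribution. The loss of degrees of freedom would add to them, but the number of centres is not given, so the addition cannot be calculated.

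**The case against.** The strongest reply is that the plan never specifies the model being criticised. Randomisation is described at practice level, but the sample size and analysis paragraphs name no level, and a multilevel model could include participant, practice and centre. The random-effects structure and the degrees-of-freedom method are ordinary content of an analysis plan that is not shown. The sentence on health centres can also be read as an open qualification of practice-level randomisation, and the article does not say that any centre with several practices was recruited.

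Much of this stands. A reader might infer that the analysis is described at practice level and that its standard errors are too small. The documents do not support either as fact: the level is not stated, and the bias also needs centres with at least two trial practices and between-centre variance above zero. A reader might also infer a single-level primary analysis, because the Effects paragraph mentions variance and regression analysis before multilevel analysis. The natural reading is that multilevel methods are how those analyses allow for clustering, so nothing shows an unadjusted analysis to be planned.

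What the reply does not remove is the point about design. The unit of randomisation is settled in this article, not deferred. It is named as the practice three times, while the allocation rule makes it the centre wherever practices share one. In a trial described as randomised by practice, unqualified references to clusters are most naturally taken to mean practices, and an analysis plan written from this text could carry the omission forward.

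**Conclusion.** The concern holds in conditional form. The named randomised unit and the allocation rule do not agree for centres with two or more trial practices, and no level is stated for the multilevel analysis or the ICC. If practice is the only level used, the true standard error is 1.00 to about 1.10 times the reported one at the stated ICC, and the real two-sided alpha is 0.05 to about 0.074. The upper end assumes that every centre has three trial practices of ten participants each and that the whole ICC lies between centres. The lower end applies if each centre holds one trial practice or centres do not differ.

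A reader might infer much larger inflation. An ICC of 0.05 lying wholly between centres would give ratios of 1.10 to 1.30 and alpha of 0.075 to 0.132 over the same k and m, but 0.05 is not the plan's value and nothing in the article supports it. Nor is the health centre the randomised unit throughout: for a stand-alone practice, the unit is the practice. The effect on the standard error at the plan's own ICC is modest; what is certain is the ambiguity about the unit.

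**What to change.** In the Randomisation section, state the randomised unit as health centre or stand-alone practice. In the analysis, make that unit the top-level random intercept of the primary multilevel model, nest practice below it if that variance can be estimated, and apply a small-sample degrees-of-freedom correction (Kenward-Roger or Satterthwaite). In the sample size section, say that the ICC and the cluster size in the design effect refer to the same unit.

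This changes wording and the model specification only. The one data item needed is the centre to which each practice belongs, and the allocation already required it. The downside is slightly wider confidence intervals.
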